### Sample size

The sample size was estimated based on the previous study reporting an effect size of 0.25 for observing the effect of CCRT on cognition [26]. With an alpha error estimate of 0.05 and power (1-β) of 0.90, 4 groups and 3 repeat measurements with a correlation among repetitive measures of 0.5 and nonsphericity correction of 1, a minimum sample size of 52 was required using G*Power 3.1.9.2 [27]. Accounting for the possibility of dropouts, the study adopts the block randomization to divide into groups with 8 patients in each block. The actual sample size of each group was 30 cases. Combining the clinical situations of each center, the Beijing and Chongqing centers were set to provide 80 and 40 patients, respectively.

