## Background

Schizophrenia is one of the most common severe mental disorders, and its etiology remains unknown. Cognitive deficits (CD), one of the core symptoms of schizophrenia, affect attention, memory, executive function, and social cognition. Among them, working memory deficits are one of the core and most characteristic of schizophrenia. These deficits are closely related to the social function, daily living ability, and academic performance of patients [1, 2].

Studies have confirmed that central control components play a fundamental role in the working memory system, which is primarily related to dorsolateral prefrontal cortex (DLPFC) function [3], but also involves the basal ganglia and hippocampus [4, 5]. An abnormal functional connection between the prefrontal lobe and other working memory-relevant areas has been hypothesized to underlie working memory deficits in schizophrenia [6, 7]. In addition, the level of brain-derived neurotrophic factor (BDNF), a protein critical for neural plasticity and synaptic signaling, was found to be decreased and closely related to impaired cognitive function in schizophrenic individuals, indicating its critical role in the pathological mechanism of schizophrenia [8–14].

Many studies have shown that repeated intensive and targeted cognitive training, such as cognitive remediation therapy (CRT), significantly improves cognitive deficits [15, 16]. Although several studies have shown that neuropsychological training methods such as CRT can significantly improve the cognitive function of patients with schizophrenia, the overall effect value is around 0.4, which is of moderate level. In particular, for working memory, the effect value was approximately 0.35. A recent systematic review showed that the overall effect of cognitive training was 0.38 and the effect on working memory was 0.29 [17]. Therefore, there is an urgent need to improve cognitive training, especially to increase the effect on working memory.

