## Methods

### Study design

This is a double-center, double-blinded, randomized, controlled intervention trial. This study was registered under Chictr.org.cn (ChiCTR2200063844). This study will be conducted from 2022 to 2024 and reported in accordance with both the Consolidated Standards of Reporting Trials (CONSORT) statement and the CONSORT statement for non-pharmaceutical interventions [24, 25].

The primary objective of this trial is to investigate the facilitation (enhancement) effect of tDCS-induced neuroplasticity changes on the direct and migratory effects of WMT on cognitive function in schizophrenia. The secondary goals are to investigate the effects of tDCS and WMT on the brain plasticity and biological markers of patients with schizophrenia, and to examine the facilitation effect of tDCS on WMT-induced changes in brain plasticity and biological markers.

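### The stated 90% power and minimum of 52 belong to the omnibus group × time test, not to the comparison that shows whether tDCS enhances WMT

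*Protocol article*

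**What the plan says.** The Sample size section takes its effect size from "the previous study reporting an effect size of 0.25 for observing the effect of CCRT on cognition". The remaining inputs are: "With an alpha error estimate of 0.05 and power (1-β) of 0.90, 4 groups and 3 repeat measurements". Repeated measures are taken to correlate at 0.5, and the sphericity factor is set to 1. The result is "a minimum sample size of 52 was required using G*Power 3.1.9.2". Neither the test nor the scale of the effect size is named. The section then sets 30 patients per arm (120 in all) to allow for dropout, without a rate.

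The Study design section gives the primary objective as to "investigate the facilitation (enhancement) effect of tDCS-induced neuroplasticity changes on the direct and migratory effects of WMT". The Abstract's hypothesis is that the combination improves cognition more than WMT by itself. The Statistical analysis section assesses the primary endpoint with a repeated-measures ANOVA on group and time. It leaves three questions to two-group comparisons after it: the tDCS effect, the WMT effect, and the promotion of WMT by tDCS.

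On plausible effects, the Background cites a recent review in which "the overall effect of cognitive training was 0.38 and the effect on working memory was 0.29". It also gives values of about 0.4 overall and 0.35 for working memory.

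**The concern.** A 6-df group × time test asks whether the four profiles over three visits differ in any way. It can be significant because both WMT arms improve and both SRT arms do not, with tDCS contributing nothing. The facilitation question is a single contrast: tDCS + WMT against sham tDCS + WMT, or the tDCS × WMT interaction. The effect size fed into the calculation also concerns training, not tDCS added to training.

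The only power figure in the article is therefore attached to a test that does not answer the primary objective. A reader who sees 52 required and 120 planned (120/52 = 2.3) will conclude that the trial is generously sized for its main question. A non-significant add-on comparison could then be taken as evidence that tDCS does not facilitate WMT.

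**Working it through.** **Inputs from the Sample size section:** alpha 0.05, power 0.90, k = 4 groups, m = 3 measurements, ρ = 0.5, nonsphericity 1, effect size 0.25, 30 per arm. **Assumptions added here:** two-sided contrasts, no dropout, no multiplicity correction.

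**1. Reproducing 52.** For the within-between interaction on the G*Power default scale, λ = f²·N·m/(1 − ρ), df1 = (k − 1)(m − 1) = 6, df2 = (N − k)(m − 1).

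- N = 48: λ = 0.0625 × 48 × 3/0.5 = 18.0, df 6 and 88, power 0.887.
- N = 52: λ = 19.5, df 6 and 96, power 0.915.

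So 52 is the smallest balanced total. Other readings of the same inputs do not give 52: the within-factor test needs 36, the between-factor test 156, and the interaction with f on the other common scales 144 to 148.

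**2. What f = 0.25 means on this test.** If gains hold at both follow-up visits, f² = (2/9) × variance of the four arm gains.

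- One arm gains d and the others nothing: variance = 3d²/16, so f² = d²/24 and d = 0.25 × √24 = 1.22 SD.
- Additive components, gains (2a, a, a, 0): variance = a²/2, so f = a/3 and a = 0.75 SD.

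**3. The same test at N = 120.** λ = 0.0625 × 120 × 3/0.5 = 45, and power exceeds 99.9%. The f detectable with 90% power is 0.158, which is 0.158 × √24 = 0.77 SD for one arm gaining alone, or 3 × 0.158 = 0.47 SD per additive component.

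**4. Contrasts that answer the objective, at 30 per arm.** In units of the outcome SD, the analysis SD is:

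- change score, one visit: √(2(1 − 0.5)) = 1.00
- baseline-adjusted, one visit: √(1 − 0.5²) = 0.866
- baseline-adjusted mean of both follow-up visits: √((1 + 0.5)/2 − 0.5²) = 0.707

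The standard error is SD × √(2/30) for the pairwise difference and SD × √(4/30) for the 2 × 2 interaction. Power is from the noncentral t with 58 and 116 df.

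| Analysis | SE, pairwise | 90% detectable, pairwise | 90% detectable, tDCS × WMT |
|---|---|---|---|
| Change score, one visit | 0.258 | 0.85 SD | 1.19 SD |
| Baseline-adjusted, one visit | 0.224 | 0.74 SD | 1.03 SD |
| Baseline-adjusted, both visits | 0.183 | 0.60 SD | 0.84 SD |

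**5. Pairwise power at the Background's values, read as SD units.**

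| Analysis | 0.29 | 0.35 | 0.40 |
|---|---|---|---|
| Change score, one visit | 20% | 27% | 33% |
| Baseline-adjusted, one visit | 25% | 34% | 42% |
| Baseline-adjusted, both visits | 35% | 47% | 58% |

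For the tDCS × WMT contrast, power over 0.29 to 0.40 SD is 12–19%, 15–24% and 20–34% respectively.

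**6. Illustration with dropout.** With 25 completers per arm (5/30 = 17% lost, an assumed rate), the pairwise detectable differences become 0.94, 0.81 and 0.66 SD, and those for the interaction 1.31, 1.13 and 0.93 SD.

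**The case against.** The calculation is right and matches the declared primary analysis: the Statistical analysis section assesses the primary endpoint by the group and time ANOVA, and that is the test 52 powers. The article never claims 90% power for the two-group comparisons. This stands, so the point is a mismatch between the powered test and the stated objective. Nor is it a complaint about condensed detail, because the article gives its sample-size basis in full.

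Three stronger readings are tempting, and the document does not support them.

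- A reader might infer that this trial can detect only 0.75 to 1.2 SD on the ANOVA. Those values are what f = 0.25 represents, and they sit near the limit of 52 patients. With 120 the omnibus thresholds are 0.77 SD for one arm alone, or 0.47 SD per additive component.
- A reader might infer that a null result is to be expected even if tDCS adds as much as training does. That holds for the one-visit analyses over 0.29 to 0.40 SD. With both visits averaged it holds at 0.29 and 0.35, but power at 0.40 is 58%.
- A reader might infer that more patients are needed. The article states no expected add-on effect. Its Background values describe cognitive training in general and carry no stated metric, so using them as the tDCS increment in SD units is an assumption.

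**Conclusion.** The concern holds as a mismatch between the powered test and the question. The 52 and the 90% are valid for the omnibus group × time interaction at f = 0.25 and do not justify the size of the trial for its primary objective. For tDCS + WMT versus sham tDCS + WMT, 90% power at 30 per arm needs about 0.85, 0.74 or 0.60 SD according to the analysis; the tDCS × WMT contrast needs about 1.19, 1.03 or 0.84 SD. None of the three analyses reaches 90% pairwise power within 0.29 to 0.40 SD; the best is 58%.

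These figures rest on the article's own correlation of 0.5, two-sided testing at 0.05, full follow-up and no multiplicity correction. Dropout, or the correction that the Statistical analysis section allows for, would lower power. The comparison with 0.29 to 0.40 also rests on the assumption that the add-on effect is of that order.

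**What to change.** Keep 120 patients and change the wording of the Sample size section.

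- State that 52 and 90% refer to the omnibus group × time interaction at Cohen's f = 0.25, with the effect size taken from a study of cognitive training, and that they do not justify the size for the facilitation question.
- For that question, put in their place the detectable differences at 30 per arm, and again after a stated dropout assumption, for tDCS + WMT versus sham tDCS + WMT and for the tDCS × WMT contrast. Label each by its analysis (change score or baseline-adjusted, one visit or both), since the values differ materially.
- State that a non-significant add-on result will be interpreted from its confidence interval and not as evidence of no facilitation. With a critical t of about 2.00 on 58 df, the 95% half-width at 30 per arm is about 2.00 × 0.258 = 0.52, 2.00 × 0.224 = 0.45 or 2.00 × 0.183 = 0.37 SD for the three analyses.

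The cost is text only: no extra patients, and no change to randomisation or assessments. The stated power becomes less favourable.

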### Randomization and blinding

Patients will be randomly divided at a ratio of 1:1:1:1 and assigned to one of the following four groups: study group (tDCS + WMT), WMT control group (tDCS + simple response training, SRT), tDCS control group (sham tDCS + WMT), and placebo control (sham tDCS + SRT). Block randomization will be performed in R (The R Foundation, Vienna, Austria) and carried out in 15 blocks of 8 participants. Each patient will be randomly assigned to the baseline group. To eliminate measurement bias, no member of the trial knew which group each patient will be assigned to, except for the caregivers who performed the tDCS treatment. Blinding will be resolved only when urgent treatment is required. Thus, the participant will be managed as off-trial.

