### Group interventions

#### *The study group (tDCS* + *WMT)*

Based on previous findings [28, 29], we will apply tDCS at 2 mA for 20 min each, with two stimulations per day separated by 3–4 h. Stimulation will be performed 5 days per week for two consecutive weeks, for a total of 20 stimulations.

We will administer tDCS using a battery-driven stimulator (EM8060, Wuhan YiMai Technology Co., Ltd., Hefei City, China) in Beijing center and a-tDCS (ActivaDose® II, ActivaTeKTM Inc., Gilroy, CA) in Chongqing center. A rectangular anodal electrode will be attached to the left DLPFC (F3 position, according to the International 10/20 system), and a rectangular cathode will be attached to the orbitofrontal cortex. The stimulation area will be wet with saline before treatment.

Each 20-min tDCS period will be immediately followed by a 1–2-min rest and 40 min of WMT (Fig. 2). The WMT tool is a computer training system based on theoretical models of working memory and cognitive processing. It was self-developed and validated in preclinical research [30]. This training employs the most typical working memory paradigm; that is, subjects try to memorize a series of continuous items (including numbers, words, and pictures) of random (unfixed) length, and judge the order of the 2–4 items presented at the end. Ten WMT sessions will be performed per week for two weeks, for a total of 20 WMT sessions.

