#### *The WMT control group (tDCS* + *SRT)*

The tDCS stimulation protocol is the same as that described in the previous section. Subsequently, SRT will be performed (Fig. 3). SRT requires no working memory processing; thus, it can be used as a comparison condition for WMT. During SRT, the patient must press a key (space) when a specific shape (such as a red triangle) is presented among many sequentially presented geometric figures. To avoid the influence of the individual items on the results, the items of the SRT are the same as those used in the WMT training,

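### One published block size of 8, with tDCS caregivers who know the group, could make some allocations foreseeable; varied and withheld block sizes would reduce this at little cost

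*Protocol article*

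**What the plan says.** The block size is given twice in the protocol article. Sample size: "the study adopts the block randomization to divide into groups with 8 patients in each block". Randomization and blinding: "Block randomization will be performed in R (The R Foundation, Vienna, Austria) and carried out in 15 blocks of 8 participants". The ratio is in the latter section: "Patients will be randomly divided at a ratio of 1:1:1:1".

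The same section says who knows the allocation: "no member of the trial knew which group each patient will be assigned to, except for the caregivers who performed the tDCS treatment". Read literally, these caregivers know the group itself and not only whether the current is active or sham.

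Sample size assigns 80 patients to Beijing and 40 to Chongqing. The article does not say whether blocks are formed within a centre or run through one shared list. It does not say whether the caregivers who give tDCS take any part in screening or enrolment.

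**The concern.** A permuted block of constant, known size becomes predictable to anyone who sees the earlier allocations in it. Once an arm has used its two places, it cannot come up again in that block, and the last place is always determined. Here both conditions are written into the plan: the size is fixed and public, and one category of staff at each site knows past allocations.

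What is at stake is selection. Some exclusion criteria under Participants call for judgement, such as poor cooperation or being unable to do the training, and these plausibly relate to cognitive performance, the primary outcome. If someone who decides eligibility or the day of entry can foresee the next arm, even without intent, the groups may differ from the start.

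**Working it through.** **Inputs.** Block size 8, 15 blocks, four arms at equal ratio (Randomization and blinding); 120 patients (Participants); 30 per arm, 80 and 40 by centre (Sample size).

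**The plan's own figures.** 15 × 8 = 120 and 120/4 = 30 per arm, as stated. 80/8 = 10 and 40/8 = 5, so whole blocks fit each centre. Each block holds 8/4 = 2 patients per arm, hence 4 active and 4 sham.

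**Assumptions for the next three steps.** The observer knows where blocks begin, sees every allocation in the block, and learns each one before the next patient is enrolled.

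**Arm known with certainty.** A place is certain when all remaining places belong to one arm.
- Last place: probability 1.
- Last two places in the same arm: 1/7.
- Sum: 1 + 1/7 = 8/7 = 1.14 per block. 15 × 8/7 = 17.1 of 120 (14.3%), of which 15 are the last patients of the blocks.

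**Active or sham known with certainty.** The probability that the last k places share one status is:
- k = 1: 1
- k = 2: 3/7
- k = 3: 3/7 × 2/6 = 1/7
- k = 4: 1/7 × 1/5 = 1/35

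The sum is 1.60 per block. 15 × 1.60 = 24 of 120 (20%).

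**Best guess** (always name the category with most places left).
- Active or sham: expected correct = 4 + 2^7/C(8,4) − 0.5 = 4 + 128/70 − 0.5 = 5.33 of 8, or 67% against 50% by chance.
- Arm: exact recursion, E(state) = max(c)/n + Σ (c_i/n) · E(state with c_i reduced by 1), where c_i are the places left in each arm and n is their sum. From (2,2,2,2) it gives 3.76 of 8, or 47.0% against 25% by chance. Over 15 blocks that is 56.4 correct against 30.

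**With varied block sizes.** Simulation of the best Bayesian guesser for arm over 120 patients, 200 runs. Sizes are drawn with equal probability, and the guesser knows the set of sizes but not their order. The sizes are illustrative assumptions.

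| Block sizes | Arm certain | Of 120 | Best guess right |
|---|---|---|---|
| 8 only (exact) | 14.3% | 17.1 | 47.0% |
| 8 and 12 | 4.8% | 5.7 | 44.5% |
| 4, 8 and 12 | 3.5% | 4.2 | 46.3% |
| 4 and 8 | 7.4% | 8.9 | 48.7% |

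Run on the fixed size of 8, the simulation returned 14.2% and 47.0%, in line with the exact values. It did not force the sizes to sum to 80 and 40. That constraint would make the last few places at each centre somewhat easier to foresee for someone counting towards the target.

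**The case against.** The best defence has three parts. First, a fixed block of twice the number of arms is a recognised choice, it gives exactly 30 per arm, and nothing in the text is contradictory. Second, a journal article commonly leaves to the full protocol who enrols, when an allocation is released and how the list is held; if those roles are separated there, most of the route to bias closes. Third, the figures are a best case for the guesser. All three stand, and they limit the point to what the article itself fixes: the constant, public block size alongside caregivers who know the group. Holding the list securely does not by itself stop someone who knows past assignments from deducing the next.

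Three stronger readings are tempting but not supported.
- *Site staff in general can foresee allocations.* Only the tDCS caregivers are said to know the group, and raters are described as blinded. The two training tasks do differ (one has patients memorise item series, in the other "the patient must press a key (space) when a specific shape (such as a red triangle) is presented"), so an onlooker might tell them apart. But the article does not say that enrolling staff watch sessions, and it says the two tasks use the same items.
- *The sham blind is weakened.* In each block every task has two active and two sham patients, so counting tasks leaves active or sham at 50:50. The caregivers learn that status at treatment anyway. Nobody new is unblinded unless they disclose it.
- *Such bias could not be repaired in analysis.* Cognition is measured at baseline and baseline enters the repeated-measures model, so selection on measured ability would be visible and partly addressed. Selection on unmeasured traits, such as motivation, could still escape.

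**Conclusion.** The point holds as an inexpensive improvement to a stated design choice, not as an error in the plan. The certain knowledge (17 of 120 for arm, 24 of 120 for active or sham) and the best-guess rates (47% and 67%) are upper figures. They require blocks filled within a centre, which 80 and 40 permit but the article does not state, and a caregiver who sees every earlier allocation. With one list shared across centres they are lower; how much lower depends on how the centres' enrolments interleave, which the article does not give. Even at the upper figures most arms remain uncertain, and bias arises only if the knowledge reaches those who screen or time enrolment.

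**What to change.** Replace the constant block of 8 with block sizes in random order, for example 4, 8 and 12, chosen to sum to 80 in Beijing and 40 in Chongqing, so that 20 and 10 patients per arm (30 in all) are kept. Withhold the sizes and their order from site staff and from published text; the public description need only say that sizes vary and are undisclosed. Avoid relying on 4 and 8 alone, which raised the best-guess rate slightly in the simulation.

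Because varied sizes cut certain knowledge but leave the best-guess rate near 45–46%, pair them with a statement that tDCS caregivers take no part in screening or eligibility decisions, if the full protocol does not already say so.

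The cost is a few lines in the R program and some protocol wording, and Trial status says recruitment had yet to begin. The downside is slightly looser balance if a centre stops mid-block: in an unfinished block of 12 two arms can differ by up to 12/4 = 3 patients, against 8/4 = 2 now.

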### MRI protocol

Brain MRI will be performed at Beijing Huilongguan Hospital. Due to limited experimental conditions, patients of Chongqing Three Gorges Hospital will not undergo MRI.

Patients will undergo a brain MRI at baseline and after treatment. MRI will be performed using an optimized protocol with a 3.0-T MRI scanner (Siemens Healthcare, Prisma, Germany). The fMRI data will be analyzed using statistical parametric mapping (SPM) (UCL Queen Square Institute of Neurology, London, UK). Changes in brain activation and connectivity between baseline and post-treatment will be compared between the four groups.

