### Statistical analysis

Analyses will be performed according to the intent-to-treat (ITT) principle. Descriptive analysis will be performed on the data collected during each assessment at baseline, post-treatment, and the 3-month follow-up. The median and range describe continuous variables, and the frequencies and percentages describe qualitative variables.

Statistical significance will be set at *P* < 0.05, and corrected for multiple comparisons, when needed. To assess our primary endpoint criterion, that is, changes in cognitive performance, the outcomes at the three time points will be compared using a repeated-measures analysis of variance (ANOVA) with time (baseline, post-treatment, and 3-month follow-up) and group (tDCS + WMT, tDCS + SRT, sham tDCS + WMT, and sham tDCS + SRT) as factors. Further comparisons between the two groups can show the simple tDCS effect, simple WMT effect, and promoting effect of tDCS on WMT. Sensitivity analyses will be used to explore the effect of missing data due to loss to follow-up and dropout.

In cases where the data do not satisfy the assumption of normal distribution, the non-parametric Mann–Whitney *U* test will be used to compare the performance improvement between the four groups. SPM will be used to analyze imaging data to detect changes in brain function caused by cognitive training.

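### Centre fixes the tDCS device and MRI access, but the primary model has no centre term and the protocol does not say whether the 15 blocks are allotted by centre

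*Protocol article*

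**What the plan says.** - **Randomisation.** Under Randomization and blinding, the ratio is equal: "Patients will be randomly divided at a ratio of 1:1:1:1". The list is "carried out in 15 blocks of 8 participants". Sample size repeats the block size: "the study adopts the block randomization to divide into groups with 8 patients in each block". Neither section says that one list serves both centres, or that blocks are allotted by centre.
- **Quotas.** Sample size: "the Beijing and Chongqing centers were set to provide 80 and 40 patients, respectively", and "The actual sample size of each group was 30 cases".
- **Device.** The study group section names the EM8060 stimulator "in Beijing center and a-tDCS (ActivaDose® II, ActivaTeKTM Inc., Gilroy, CA) in Chongqing center".
- **Imaging.** MRI protocol: "patients of Chongqing Three Gorges Hospital will not undergo MRI".
- **Primary model.** Statistical analysis specifies a repeated-measures ANOVA with time at three levels "and group (tDCS + WMT, tDCS + SRT, sham tDCS + WMT, and sham tDCS + SRT) as factors". Centre is neither a factor nor a covariate.

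**The concern.** Centre is more than an administrative label here. It decides which machine delivers the stimulation and whether a patient contributes to the imaging outcomes. Two things follow.

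If allocation is not balanced within centre, the arms can hold different mixes of the two devices, and the Beijing-only imaging comparison can lose its planned 20 per arm.

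If the model has no centre term, any difference between centres in how much patients change over time has nowhere to go but the error term or, where the arms are unbalanced by chance, the arm contrasts. Nor does the stated analysis show whether the tDCS effect is similar on the two devices, although the trial's main question is what tDCS adds.

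**Working it through.** **1. Which test the plan is sized for.** Inputs from Sample size: f = 0.25, alpha 0.05, power 0.90, k = 4 groups, m = 3 measurements, correlation 0.5, nonsphericity correction 1. For the group-by-time interaction:

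- noncentrality = f² × N × m / (1 − 0.5) = 0.0625 × 52 × 3 / 0.5 = 19.5
- df1 = (4 − 1)(3 − 1) = 6 and df2 = (52 − 4)(3 − 1) = 96
- power = 0.915, and 52 is the smallest multiple of four that reaches 0.90.

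The stated 52 is reproduced. The within-subject main effect would give 36 and the between-subject main effect 156, so the sized test is group by time. In that test a constant centre difference in level cancels. Only a centre or device difference in change matters.

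**2. Block arithmetic.** 15 × 8 = 120, 80 / 8 = 10 and 40 / 8 = 5. Each block holds two patients per arm. Ten blocks in Beijing give 20 per arm and five in Chongqing give 10 per arm, so the stated scheme is fully compatible with exact balance by centre.

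**3. If one list served both centres.** Assumption: 40 of the 120 list positions fall to Chongqing at random. For one arm of 30:

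- variance of the Chongqing count = 40 × (30/120) × (90/120) × (80/119) = 5.04, so SD = 2.25
- 95% range in Chongqing is 6 to 14 around 10, hence 30 − 14 = 16 to 30 − 6 = 24 in Beijing around 20.

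Simulation of 50,000 such lists agrees (SD 2.25, same range) and gives the gap between the largest and smallest arm within a centre:

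| Quantity | Result |
|---|---|
| Mean gap | 5.3 |
| P(gap ≥ 4) | 0.78 |
| P(gap ≥ 6) | 0.44 |
| P(exactly 10 per arm in Chongqing) | 0.007 |
| Active minus sham in Chongqing, 95% range | −10 to +10 of 40 |

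With the blocks split 10 + 5, the gap is zero in every simulated list.

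**4. What that imbalance could do.** Let δ be the centre difference in change, in SD units. The documents give no value, so 0.25 and 0.5 are shown as assumptions.

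- Two arms: the difference in Beijing counts has variance 2 × 5.04 × (1 + 1/3) = 13.4, SD 3.67, so the 95% limit is about 7 patients. The shift is 7/30 × δ = 0.06 SD at δ = 0.25 and 0.12 SD at δ = 0.5.
- Active against sham: 10 of 40 is a 25 to 15 split, so the shift is (25 − 15)/60 × δ = 0.04 to 0.08 SD.

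These are 95% limits of a chance deviation with mean zero.

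**5. Imaging set.** Only Beijing patients are scanned, so imbalance changes arm sizes but does not mix centres or devices. At 16 against 24, 1/16 + 1/24 = 0.104, compared with 1/20 + 1/20 = 0.100. The contrast variance rises by about 4%.

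**6. If blocks are allotted by centre.** The shifts in step 4 vanish at full recruitment. Any centre difference in change then sits in the error term of a model that leaves out the factor used to stratify.

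**The case against.** The strongest reply is that the protocol article does not say stratification is absent. It is silent, and quotas of 80 and 40 are exact multiples of 8, as allotment by centre would produce. A condensed article may leave this, and covariates, to a fuller plan. The part about the list stands: a missing centre stratum is not established, and the imbalance figures hold only under the shared-list assumption. The part about the model is weaker, because Statistical analysis names its factors explicitly and centre is not among them.

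Four stronger readings are tempting and are not supported:

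- **Bias.** A reader might infer that the arm comparison is systematically biased. Under randomisation, chance imbalance by centre adds noise.
- **Level differences.** A reader might infer that any centre difference in scores inflates the error of the primary test. A constant difference in level drops out of group by time (step 1).
- **Different raters.** A reader might infer that different raters at each centre affect cognition. Neuropsychological assessments places four physicians at each centre for the symptom scales only. The cognitive outcomes are assigned to trained neuropsychologists, with no statement that they differ by centre in a way that matters.
- **Concealment.** A reader might infer that a published fixed block lets the unblinded tDCS caregivers steer allocation. Foreseeing an assignment is harmful only if they can influence enrolment, and the document gives them no such role. Predictability also presupposes that staff see every allocation in a block, which fits site-specific blocks, whereas the imbalance figures need a shared list. The two cannot be added.

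**Conclusion.** The point holds as a modest, inexpensive weakness in the stated model, together with an ambiguity about the list.

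On either reading of the randomisation text, two devices are pooled with no centre term and no stated look at whether the tDCS effect differs between them. With a shared list, Beijing arms would run from about 16 to 24 (P(gap ≥ 6) = 0.44), and a centre difference in change of 0.25 to 0.5 SD could move a pairwise contrast by up to about 0.06 to 0.12 SD by chance. With blocks allotted by centre, that disappears and only the omitted stratification factor remains.

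This rests on three assumptions: positions falling to centres at random in the shared-list case, quotas being met, and the illustrative δ. The sample size of 52 and the planned 120 are unaffected.

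**What to change.** 1. State that the existing 15 blocks of 8 are allotted by centre, 10 to Beijing and 5 to Chongqing. This gives exactly 20 and 10 per arm at full recruitment. If a centre stops mid-block, arms there differ by at most two, because each block holds two per arm.
2. Add centre and centre-by-time to the primary repeated-measures model.
3. Report the tDCS effect separately by centre as a check for device differences, labelled descriptive. With 40 patients in Chongqing it has low power, and device cannot be separated from other centre differences.

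The cost is one sentence and two model terms. With two centres and three time points these take 1 and 2 degrees of freedom. At N = 120 the between-subject error goes from 120 − 4 = 116 to 115, and the within-subject error from 116 × 2 = 232 to 230. N does not change. Trial status says recruitment has yet to begin. The list should be settled before then, since stratification cannot be added after enrolment.
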